## 9.4 Analysis of Safety

We will conduct a safety analysis on the safety population. Worst toxicity grades per subject will be tabulated for selected AEs and laboratory measurements. All recorded AEs, SAEs and AEs leading to study therapy discontinuation will be listed and tabulated. Vital signs and clinical laboratory test results will be listed and summarized by treatment arms. Any significant physical examination findings, ECG results, and clinical laboratory results will be listed.

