# Study Design

This is a multicenter, double-blinded, placebo-controlled, randomized clinical trial in advanced HCC patients with extrahepatic metastasis. Subjects will be randomly assigned to one of the two arms, either ATRA+FOLFOX or FOLFOX alone. Our study has been registered at <http://www.chictr.org.cn> (ID: ChiCTR-IIR-17012916).

**
[figure not shown]
**

After screening for eligibility and signing of informed consent, qualified subjects will be randomized in a 1:1 ratio to receive ATRA+FOLFOX4 (Group A) or Placebo + FOLFOX4 (Group B). Randomization will be stratified by site and treatment assignments will remain blinded throughout the study.

Names of Therapeutic Agents:

- All-trans-Retinoic Acid (ATRA)
- Oxaliplatin (OXA)
- 5-Fluorouracil (5FU)
- Leucovorin (LV)

Mode of Administration:

ATRA+FOLFOX4 (Group A): ATRA 20 mg oral 3 times/day for 3 days prior to the initiation of chemo (FOLFOX4). ATRA will be discontinued at the end of FOLFOX4(OXA 85mg/m2 iv day1, LV 200mg/m2 iv day1 and day 2, 5FU 400mg/m2 iv bolus at hour 2 and then 600 mg/m2 iv over 22 hours on day 1 and day 2, once every 2 weeks) and a total of 6 cycles were performed. Placebo+FOLFOX4 (Group B):The placebo (replacing ATRA) will be given orally 3 times/day for 3 days prior to the chemo. The placebo will then be discontinued at the end of FOLFOX4 and a total of 6 cycles were performed. The follow-up phase began once a patient terminated the treatment phase.

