Subjects will be evaluated for tumor response every 4 weeks. Tumor imagine evaluation will be performed by either computerized tomography (CT) scan or MRI. Progression will be determined based on modified RECIST criteria for HCC. Drug therapy will be continued until unacceptable toxicity or disease progression occurs. If investigator determines the subject is benefiting from the blinded study drug and the subject is willing to continue the blinded study drug, the treatment may be continued beyond radiographic progression. Choice of subsequent therapies in case of progressive disease will be at the best discretion of the investigator, which should be beneficial to subjects overall. Subsequent treatments for HCC will be collected in the follow-up period. Requests for un-blinding will only be granted for emergency medical management. Subjects who have discontinued study therapy due to study drug toxicity or any reason other than confirmed tumor progression will continue to have tumor assessments every 4 weeks until documented radiographic tumor progression. All randomized subjects will be followed for overall survival until the required number of events has been reached.

Discontinuation of Subjects from Treatment: subjects must discontinue the investigational agents for any of the following reasons:

1. Withdrawal of informed consent (subject’s decision to withdraw for any reason).
2. Any clinical adverse event (AE), laboratory abnormality or intercurrent illness which,
3. in the opinion of the investigator, indicates that continued participation in the study is not in the best interest of the subject.
4. Pregnancy.
5. Loss of ability to freely provide consent due to either a psychiatric or physical (e.g. infectious disease) illness.
6. Disease progression*

* Note: If investigator determines the subject is benefiting from the blinded study drug (for example: subject may be experiencing symptomatic improvement at the time of documented radiographic progression) and the subject is willing to continue the blinded study drug, the treatment may be continued beyond radiographic progression.

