## 7.3 Safety Endpoints

Study drug toxicities will be assessed continuously, which include vital sign, physical exam, neurological exam, EKG, Echo, clinical lab tests (hemoglobin, hematocrit, red blood cell, total leukocyte count with differential, platelet count, AST, ALT, total bilirubin, direct bilirubin, alkaline phosphatase, lactate dehydrogenase (LDH), creatinine, BUN or urea, blood glucose, total protein, albumin, sodium, potassium, chloride, total calcium, phosphorus, magnesium, ammonia, and AFP) and specialty exams (chest X-ray, CT, MRI, Bone Scan, etc.). All the adverse events will be evaluated according to the NCI CTCAE (Version 4.0), on a continuous basis while the subject is on study. Scheduled evaluations will occur every 4 weeks.

| **Parameters** | **Definitions** |
| --- | --- |
| **Complete Response (CR)** | Complete disappearance of extrahepatic metastatic lesions under the contrast-agent enhancement in the arterial phase of spiral CT or MRI. CR must be confirmed by a second evaluation no less than 4 weeks after the date the CR was first obtained. |
| **Partial Response (PR)** | Decrease of > 30% in the sum of the longest diameters (SLD) of extrahepatic metastatic lesions taking reference the baseline SLD. PR must be confirmed by a second evaluation no less than 4 weeks after the date the PR was first obtained. |
| **Stable Disease (SD)** | Failure to meet criteria for complete or partial response, in the absence of progressive disease. |
| **Progressive Disease (PD)** | - Increase of > 20% in the SLD of extrahepatic metastatic lesions taking reference the smallest SLD of target lesions recorded since the treatment started. If the 20% or more increase is observed in two consecutive determinations, the date of PD is the date of the first evaluation. OR - New extrahepatic metastatic lesions with the longest diameter of at least 10 mm confirmed by contrast-enhanced spiral CT or MRI imaging. OR - Appearance of one or more new extrahepatic lesions of any size. OR - Appearance of more intrahepatic lesions, expanding existing lesions (including portal vein emboli). |
|  |  |

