## 8.4 Collection and Reporting

Adverse events can be spontaneously reported or elicited during open-ended questioning, examination, or evaluation of a subject (to prevent reporting bias, subjects should not be questioned regarding the specific occurrence of one or more AEs).

If known, the diagnosis of the underlying illness or disorder should be recorded, rather than its individual symptoms. The following information should be captured for all AEs: onset, duration, intensity, seriousness, relationship to study drug, action taken, and treatment required. If treatment for the AE was administered, it should be recorded on the appropriate CRF page. The investigator shall supply the sponsor and Ethics Committee with any additional requested information, notably for reported deaths of subjects. Completion of supplemental CRFs may be requested for AEs and/or laboratory abnormalities that are reported/identified during the course of the study.

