**5.3 Safety Analyses**

We report absolute frequencies of events as well as percentages per group separately by safety measure without imputed values for missing in the full analysis set.

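### The safety tables take in all AEs recorded while patients are on study, with no on-treatment window in the available text, so study-drug toxicity can be mixed with later therapy and disease decline.

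*Combined protocol and SAP*

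**What the plan says.** The second item under Study Objectives in the protocol is the safety of ATRA given with FOLFOX.

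- **Collection.** Protocol 7.3 and SAP 4.3 have AEs evaluated "on a continuous basis while the subject is on study". The Schedule of Events marks AEs/SAEs and laboratory tests at every visit from M1 to M12. It shows no end-of-treatment visit.
- **Treatment length.** Study Design (and SAP 1.4) gives the regimen as "once every 2 weeks) and a total of 6 cycles were performed", and adds: "The follow-up phase began once a patient terminated the treatment phase". Further on, the protocol's Study Design section also says: "Drug therapy will be continued until unacceptable toxicity or disease progression occurs". It allows continuation past radiographic progression in some cases.
- **Later therapy.** Treatment after progression is left to the investigator, and "Subsequent treatments for HCC will be collected in the follow-up period".
- **Tabulation.** Protocol 9.4: "All recorded AEs, SAEs and AEs leading to study therapy discontinuation will be listed and tabulated". The same section tabulates each subject's worst grade for selected AEs and laboratory measurements. SAP 5.3: "We report absolute frequencies of events as well as percentages per group separately by safety measure".
- **Data captured per AE.** Protocol 8.4 lists "onset, duration, intensity, seriousness, relationship to study drug, action taken, and treatment required".

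The available text contains no treatment-emergent definition, no cut-off after last dose or at new therapy, no table restricted to related events and no exposure-adjusted rate. The part of the SAP between sections 2.2 and 4 could not be seen. Protocol 9.4 can be read in full and has none of these.

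**The concern.** Under these rules, a grade 4 laboratory value at month 9, recorded while a patient is on another anticancer drug or has a failing liver, can become that patient's worst grade in the randomised arm. Such events say little about ATRA. They can dilute a real difference between arms, or create an apparent one, because the time available to record them and the deaths among them both depend on survival, which the trial expects to differ. A reader of the tables could not separate the two sources. What is at stake is the answer to the safety objective; the primary OS test is not affected.

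**Working it through.** **1. The plan's own figure.** The safety sections contain no calculation, so the survival inputs come from protocol 9.1 and SAP 1.6: OS 14.9 v 8.2 months, two-sided α 0.05, power 80%, 10% for losses, total 106. HR = 8.2/14.9 = 0.550. Freedman events = ((1+HR)/(1−HR))² × (1.960+0.842)² = 93.3, so 94, or 47 per arm; 47/0.90 rounds up to 53 per arm, 106 in total. The figure reproduces. Below, 14.9 and 8.2 are taken as medians of exponential survival, which is an assumption.

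**2. Windows.** Six 2-week cycles = 84 days = 2.76 months. A window of 84 + 30 = 114 days = 3.75 months is used for illustration; the 30 days are not in the documents.

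**3. Time alive.** λ = ln 2/median = 0.0465 (ATRA) and 0.0845 (placebo) per month. Mean time alive to t = (1 − e^(−λt))/λ.

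| Period | ATRA | Placebo | Ratio |
|---|---|---|---|
| 12 months | 9.20 | 7.54 | 1.22 |
| 12 weeks + 30 days | 3.44 | 3.21 | 1.07 |
| 12 weeks | 2.59 | 2.46 | 1.05 |

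Under the six-cycle text, the share of time alive to month 12 that lies outside the 114-day window is 1 − 3.44/9.20 = 63% (ATRA) and 1 − 3.21/7.54 = 57% (placebo). The 12-month ratio falls to 1.13 at an HR of 0.71 and to 1.00 with equal survival.

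**4. Non-fatal AEs, same constant rate h in both arms.** The documents give no rate, so a range is shown. P(at least one by t) = h/(h+λ) × (1 − e^(−(h+λ)t)).

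| h per month | By month 12, ATRA v placebo | In 114-day window |
|---|---|---|
| 0.05 | 35.5% v 29.8% | 15.7% v 14.7% |
| 0.10 | 56.5% v 48.3% | 28.8% v 27.0% |
| 0.20 | 76.9% v 68.0% | 48.9% v 46.1% |

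**5. SAEs with death counted.** Protocol 8.2 lists death as an SAE. Expected deaths by month 12 = 1 − e^(−12λ) = 43% v 64%. P(any SAE by month 12) = 1 − e^(−12(h+λ)):

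| h per month | ATRA v placebo |
|---|---|
| 0.02 | 55.0% v 71.5% |
| 0.05 | 68.6% v 80.1% |
| 0.10 | 82.8% v 89.1% |

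The order of the arms reverses.

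**6. Higher rates on treatment.** Let the non-fatal rate be h₁ inside the 114 days and 0.10 per month afterwards.

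| h₁ per month | By month 12 | In window |
|---|---|---|
| 0.5 | 85.9% v 80.7% | 79.7% v 76.0% |
| 1.0 | 94.6% v 91.3% | 93.7% v 90.6% |

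When most patients have an event during chemotherapy, the window barely changes the any-AE row. It matters more for less common events, which are closer to the low-rate rows of step 4.

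**The case against.** The strongest reply is that the plan already ties AEs to study drug. Protocol 8.1 defines an AE partly by its timing relative to product use, 8.3 and 8.4 require onset and a related/not-related judgement for every event, and assessments are blinded. Worst grades are limited to selected AEs, and AEs leading to discontinuation of study therapy are by nature treatment-linked. The safety summary is descriptive, with no test planned.

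The schedule also need not apply literally to every patient. It marks CT/MRI to M12 for all, whereas Study Design requires imaging after an early stop only until progression, and its account of what continues after stopping does not mention AEs. Finally, an unseen part of the SAP might contain a window.

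Some of this stands. AEs leading to discontinuation are largely unaffected, collection to M12 in every patient is an inference from the grid, and absence can be claimed only for the available text. The rest does not cure the problem. The definition in 8.1 sets no number of days and does not require causality. Relatedness is recorded, but no planned table uses it. Two programmers working from 9.4 could produce different tables.

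A reader might go further and infer that the plan counts more events against the longer-surviving arm, so that ATRA would look falsely toxic. The documents do not support that as a general statement. It follows for non-fatal events that accrue with time alive, but it reverses once death is counted as an SAE (step 5), and events of terminal decline would also tend to fall on the arm that dies earlier.

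**Conclusion.** The concern holds as a gap in definition with an unpredictable effect. As the available text stands, events after study treatment, including those under other HCC therapy, can enter the main safety tables, and the arm comparison then depends on survival. Neither a bias against ATRA nor one in its favour is established.

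Under the planning assumptions, the 12-month tables rest on 22% more time alive in the ATRA arm, against 7% more within 12 weeks plus 30 days. The resulting gap in any non-fatal AE by month 12 is about 6 to 9 percentage points at constant rates of 0.05 to 0.20 per month. The window changes little if on-treatment rates are high. With death included, the gap in any SAE runs the other way, by about 6 to 16 points at 0.02 to 0.10 per month.

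These figures assume exponential survival, equal AE rates in the two arms and AE recording to month 12 or death. The 57% to 63% of time outside the window also assumes six cycles. Study Design states both six cycles and treatment until toxicity or progression, and these statements must be reconciled. Duration alters the size of the problem but does not remove it, since patients who stop early can still have AEs recorded afterwards. The point merits a change to the plan because it bears on a stated objective.

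**What to change.** In protocol 9.4 and SAP 5.3:

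1. Make the main AE, SAE and worst-grade tables (including laboratory grades) treatment-emergent: from first dose of ATRA/placebo or FOLFOX4 to a sponsor-set number of days after last dose (for example 30), or to the start of new anticancer therapy if earlier.
2. Add exposure-adjusted rates. If treatment runs to progression, the window is longer in the arm that progresses later, so a window alone does not equalise observation.
3. Tabulate later events separately, but keep late SAEs judged related in the main table.
4. Reconcile the two statements of treatment duration in Study Design, and state how long AEs are collected after study treatment stops.

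A window tied to each patient's own last dose works under either statement of duration. A window that starts at first dose also needs one safety population: SAP 2.1 equates it with the intention-to-treat set, SAP 2.2 requires at least one dose, and SAP 5.3 names the full analysis set.

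The cost is a wording change and a programming flag. AE onset, concomitant medication and subsequent HCC therapy are already collected. The downside is that unrelated late events move to a separate table; none are lost.

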# Schedule of Events

| **Visits** | **Enrollment & Randomization** | **M1** | **M2** | **M3** | **M4** | **M5** | **M6** | **M7** | **M8** | **M9** | **M10** | **M11** | **M12** |
| --- | --- | --- | --- | --- | --- | --- | --- | --- | --- | --- | --- | --- | --- |
| **Identification** | X |  |  |  |  |  |  |  |  |  |  |  |  |
| **Screen by inclusion/exclusion criteria** | X |  |  |  |  |  |  |  |  |  |  |  |  |
| **Informed Consent Form** | X |  |  |  |  |  |  |  |  |  |  |  |  |
| **Initial Assessment (history/physical/lab/imaging)** | X |  |  |  |  |  |  |  |  |  |  |  |  |
| **Assessment – History/Physical** | X | X | X | X | X | X | X | X | X | X | X | X | X |
| **CT Scan/MRI** | X | X | X | X | X | X | X | X | X | X | X | X | X |
| **Laboratory Tests** | X | X | X | X | X | X | X | X | X | X | X | X | X |
| **Quality of life Questionnaires** | X | X | X | X | X | X | X | X | X | X | X | X | X |
| **Overall Survival** |  | X | X | X | X | X | X | X | X | X | X | X | X |
| **Tumor Progression Assessment** |  | X | X | X | X | X | X | X | X | X | X | X | X |
| **Concomitant Medication** | X | X | X | X | X | X | X | X | X | X | X | X | X |
| **AEs/SAEs** |  | X | X | X | X | X | X | X | X | X | X | X | X |

**11. Discussion**

85% of HCC patients present with an advanced disease stage at diagnosis, and a large number of patients diagnosed with early-stage disease eventually experience recurrence**^23^**. Sorafenib is the only drug approved by FDA that extends the overall survival time of patients with advanced HCC by approximately three months in the Barcelona Clinic Liver Cancer (BCLC) staging classification. The response rate is only 2-3% and the acquisition of a CR was rarer**^24^**. In contrast to other solid cancer, chemotherapy has not been used routinely in HCC before because of the toxicity and high incidence of chemo-resistance.

However, with the constant progress of chemotherapeutics especially platinum drugs, recent trials have proved that chemotherapy may have a role in the treatment of advanced HCC. In one recent study**^25^**, metronomic chemotherapy including 5-FU and cisplatin was associated with more favorable outcomes in terms of overall survival than was sorafenib in advanced HCC (158 days vs. 117 days, p=0.029). In the EACH study**^14^**, FOLFOX showed an improvement in median overall survival and similar rate of AEs compared with doxorubicin (6.40 months vs 4.97 months, p=0.07), and has been established as an option in the treatment of advanced HCC.

Despite the advances in systemic chemotherapy, drug resistance is still an obstacle to acquire further improvement. Increasing evidence has shown that tumor initiating cells (TICs) exhibit greater resistance to conventional chemotherapies than non-TICs. It is well known that ATRA is one of the strongest and the most thoroughly studied differentiation inducers which could induce differentiation of kinds of tumor cells including stem cells. Our previous studies**^16,17^** showed that ATRA could induce differentiation of HCC TICs via TS2/AKT pathway and combined treatment with ATRA and Cisplatin could improve therapeutic effect, due to elimination of TICs via ATRA-induced differentiation in vivo and in vitro.  Therefore, our hypothesis holds that a ATRA/FOLFOX to the extrahepatic metastasis might be useful and no prospective trial has been investigated in this setting so far.

**1. Study Background**

**1.1 Study Objective**

The presence of extrahepatic metastasis (EHM) is a major cause of the death of hepatocellular carcinoma (HCC) patients, but there is no standard treatment and even no prospective clinical trials have even been designed specifically for HCC with EHM till now. Systemic treatment is the only recommended therapy according to the BCLC staging system and the Chinese Guidelines for The Diagnosis and Treatment of Hepatocellular Carcinoma. But the expected median survival time was only 6 to 10 months. All-Trans Retinoic Acid (ATRA) is known as one of the strongest differentiation inducers which could induce differentiation of several types of tumor cells including stem cells. Our previously studies showed that ATRA potentiates the chemotherapeutic effect of cisplatin/oxaliplatin. Our retrospective clinical studies also confirmed the efficacy of combination therapy which could prolong the median OS to 14.0 month.

Therefore, the primary objective of this trial is to study the effect of ATRA-FOLFOX4 on the efficacy of treatment of HCC with EHM.

**1.2 Primary hypothesis**

The primary hypothesis of the project is that ATRA-FOLFOX4 leads to a better overall survival compared to FOLFOX4 alone.

**1.3 Secondary hypothesis**

- ATRA-FOLFOX4 leads in HCC patients with EHM compared to FOLFOX4 alone to better progress-free survival.
- To determine the safety of ATRA in the combination with FOLFOX

**1.4 Study design**

This is a multicenter, double-blinded, placebo-controlled, randomized clinical trial in advanced HCC patients with EHM. The randomization schedule was generated by an independent statistician using randomization block method in SAS 9.4. Eligible subjects enrolled in the study all received a unique subject identification number and were randomly assigned to a treatment group ATRA- FOLFOX4 or FOLFOX4 alone in a ratio of 1:1 (Website: http://pro32.irtone.com/). Both subjects and investigators did not know the true treatments and were blinded until emergency un-blinding and after database lock. Our study has been registered at <http://www.chictr.org.cn> (ID: ChiCTR-IIR-17012916).

After screening for eligibility and signing of informed consent, qualified subjects will be randomized in a 1:1 ratio to receive ATRA+FOLFOX4 (Group A) or Placebo + FOLFOX4 (Group B). Randomization will be stratified by site and treatment assignments will remain blinded throughout the study.

Names of Therapeutic Agents:

- All-trans-Retinoic Acid (ATRA)
- Oxaliplatin (OXA)
- 5-Fluorouracil (5FU)
- Leucovorin (LV)

Mode of Administration:

ATRA+FOLFOX4 (Group A): ATRA 20 mg oral 3 times/day for 3 days prior to the initiation of chemo (FOLFOX4). ATRA will be discontinued at the end of FOLFOX4(OXA 85mg/m2 iv day1, LV 200mg/m2 iv day1 and day 2, 5FU 400mg/m2 iv bolus at hour 2 and then 600 mg/m2 iv over 22 hours on day 1 and day 2, once every 2 weeks) and a total of 6 cycles were performed. Placebo+FOLFOX4 (Group B):The placebo (replacing ATRA) will be given orally 3 times/day for 3 days prior to the chemo. The placebo will then be discontinued at the end of FOLFOX4 and a total of 6 cycles were performed. The follow-up phase began once a patient terminated the treatment phase.

A more detailed description of the in- and exclusion criteria can be found in the in- and exclusion criteria below.

**1.5 In- and exclusion criteria**

The treatment candidates were defined as having the following characteristics.

- General inclusion criteria:

Male and female, ages 18-75 and above, with documented advanced HCC; Child-Pugh Class A; With confirmed extrahepatic metastatic lesions located in lung, bone, abdominal metastasis including lymph nodes; ECOG performance status Grade 1 or less; life expectancy 3 months; Liver and renal lab test must meet the following ranges: Total bilirubin equal or less than 1.5 times of upper normal limit (UNL) defined by each clinical lab in each site, ALT and AST less than 2.5 times of times of upper normal limit (UNL) defined by each clinical lab in each site, Serum Creatinine equal or less than 1 times of upper normal limit (UNL) defined by each clinical lab in each site, Endogenous creatinine clearance rate >50ml/min (calculated with Cockcroft-Gault formulation). Other lab tests: Hemoglobin ≧ 90g/L, Platelet Count ≧75 ˟10 9/L, WBC Count ≧3.5 ˟10 9/L. Good cardiac function, no myocardial infarction within 6 months; well controlled hypertension and coronary heart disease if any.

- General inclusion criteria:

No extrahepatic metastatic lesion found; decompensated liver function or hepatic encephalopathy; egnant or breast-feeding women; ucontrolled hypertension even with medication; pients with hemorrhagic disorders or active bleeding or sepsis; history of HIV infection and AIDS or other acute or chronic disease; active or uncontrolled severe infections; CHF NYHA class > 2, active CAD or cardiac ischemia, uncontrolled cardiac arrhythmias even with anti-arrhythmic therapy; unable to take oral medication; low compliance judged by investigators; seizure disorder requiring medication (such as steroids or anti-epileptics); history of drug abuse, or mental disorders which could compromise compliance; any other conduction which may jeopardize patient safety and compliance.

